**8.3 Pharmacoeconomic evaluation**

Calculate the cost/utility of the protocol of combinations of different drugs, and ascertain the optimal protocol of hospital treatment of patients with acute cerebral stroke. As for the costs, only the direct cost is collected, and the indirect cost and implicit cost are not collected. The direct costs in the study include:

- Direct medical cost (including the dug expense, examination expense, laboratory test expense, diagnosis and treatment expense, nursing expense and bed expense)

Discharge visit (Visit 3): Collect the direct medical cost according to the fees list of patients on discharge.

Visit 4 and visit 5: collect the direct medical costs by inquiring the patients or their families.

- Direct non-medical cost (including transportation expense, nutrition expense, family accompanying expense)

Directly collect the transportation costs and the nutrition costing by inquiring the patients or their families, and collect the nursing fees of the families by inquiring the families of the days/hours of downtime and calculating the fees through multiplying the days/hours by the local average wage.

In the utility analysis, quality-adjusted life years (QALYs) are used as the index of health outcome. The cost unit is Renminbi (RMB).

The QALY values are calculated through the utility value acquired by EQ-ED (evaluated on day 0 before treatment, at discharge,on 90 ± 14 days after treatment, 360 ± 28 days after treatment), and the pathway of the quality of life can be acquired by connecting the utility values on day 0, at discharge, on 90 ± 14 days after medication. With the time required for improving the quality of life as weights, we will get the QALY values. See the reference for the calculation method. [[14]](#bookmark16)

The EuroQol-5 Dimensions (EQ-5D) consists of two parts: the questionnaire and the conversion table of utility values. The questionnaires results can be used to describe the health status of the population and access to the EQ-VAS scores, and the EQ-5D index score can be further acquired by using the the time trade off (TTO) conversion table of utility values. Given that there is no suitable TTO conversion table of utility values in Chinese, the conversion table of utility values for Japanese is used to acquire the EQ-5D index scores. The following is the TTO conversion table of utility values in Japanese [[15]](#bookmark17):

| **Dimensions of EQ-5D** | **Level** | **Index** |
| --- | --- | --- |
| Mobility | 1 | 0.000 |
|  | 2 | 0.075 |
|  | 3 | 0.418 |
| Self Care | 1 | 0.000 |
|  | 2 | 0.054 |
|  | 3 | 0.102 |
| Usual Activities | 1 | 0.000 |
|  | 2 | 0.044 |
|  | 3 | 0.133 |
| Pain or discomfort | 1 | 0.000 |
|  | 2 | 0.080 |
|  | 3 | 0.194 |
| Anxiety or depression | 1 | 0.000 |
|  | 2 | 0.063 |
|  | 3 | 0.112 |
| Constant | 0.152 | |

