| **Inclusion criteria** | 1. Age≥18 years 2. In conformity with the diagnosis criteria (draft) of China 2014 Guidelines for Diagnosis and Treatment of Ischemic Cerebral Stroke 3. The onset time of thrombolytic patients are within the time window of thrombolysis 4. The onset time of thrombolytic patients are within one week 5. The patients or legal guardians can understand and sign the informed consent form |
| **Exclusion criteria:** | 1. Cranial CT/MRI can display the presence of cerebral hemorrhage 2. The expected survival time of patients less than three months because of complicated serious systemic diseases i 3. the patients cannot provide continuous follow-up information by investigator judgments |
| **Primary efficacy endpoint** | The proportion of patients with good prognosis (mRS=0-2 points) at 90 days after treatment |
| **Secondary efficacy endpoint** | 1. The proportion of patients with poor prognosis (mRS= 3-5 points) and death (mRS=60 points) at 90 days after treatment 2. The changes in National Institutes of Health Stroke Scale (NIHSS) at discharge from baseline 3. The changes in EQ 5 visual analogue scale (EQ-5D, VAS) at discharge from baseline |
| **Safety parameters** | 1. Incidence rate of symptomatic intracranial hemorrhage transformation during the hospital stay 2. Adverse events 3. Vital Signs 4. Laboratory tests (blood routine test, blood glucose, blood lipids, liver and renal functions, myocardial enzymes, serum electrolytes, and coagulation function) 5. ECG examination |
| **Exploratory analysis** | Analysis on the prescriptions of acute specific treatment for different TOAST types  Stroke recurrence rate and incidence rate of post-stroke dementia at 90 days after treatment |
| **Pharmacoeconomic evaluation** | Calculate the cost/utility of the protocol of combinations of different drugs, and ascertain the optimal protocol of hospital treatment of patients with acute cerebral stroke.  As for the costs, only the direct cost is collected, and the indirect cost and implicit cost are not collected. The quality adjusted life years (QALYs) is adopted for the utility analysis as the health outcome parameter. |

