The acute ischemic cerebral stroke is the main cause that leads to the long-term disenabling, thus bring severe economic burdens[[10]](#bookmark11) to society and patient's family. Therefore, the performing of pharmacoeconomic evaluation on the different therapeutic regimens during the acute phase of cerebral stroke and the seeking of one or more kinds of drug therapeutic regimens with a high price/performance ratio which are suitable to the domestic conditions are of a higher social value. In the field of cerebral stroke treatment, currently there is rare prospective pharmacoeconomic evaluation domestically. Unlike the domestic cerebral stroke study fields which often adopt the cost effectiveness analysis (CEA)[[11]](#bookmark12), this study utilizes the cost utility analysis (CUA) for economic evaluation, the quality adjusted life years (QALYs) serves as the health outcome index, and the advantage of this method lies the measurement of life quality and the improvement of life-span (longevity) [[12]](#bookmark13). Considering the original intention of using this study as the registration study as well as the difficulty in expense collection, this study only collects the direct costs during the patient's hospitalization, and does not collect the indirect cost and implicit cost.

To sum up, this objective of this study is to analyze status quo of different drug combinations in the real world, evaluate the efficacy of different drug combination regimens in treating acute ischemic cerebral stroke, and perform cost-utility analysis. It aims to provide reference for a wide range of clinicians when selecting medications to treat acute ischemic cerebral stroke.

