**2 Study objective**

Primary study objective:

Analysis of current treatment situation in acute phase of acute ischemic stroke in real-world settings。

Secondary study objectives

(1) Comparison of effects of various drug combinations in treatment of acute ischemic stroke in real-world settings.

(2) Analysis of cost-utility of various drug combinations in treatment of acute ischemic stroke.

(3) Analysis of occurrences of complications and adverse events during treatment in hospital in patients with acute ischemic stroke.

(4) Analysis of effects of TOAST typing on specific therapy regimens in acute phase of acute ischemic stroke.

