**10.5 Pharmacoeconomic analysis**

The cost - utility evaluation methods are used for the pharmacoeconomic analysis of the drug and the sensitivity analysis for the cost and utility indexes.

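### Choosing an optimal regimen on cost/utility, read as written, compares average cost per QALY; an incremental analysis with stated uncertainty should replace it

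*Protocol*

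**What the plan says.** The pharmacoeconomic row of the Protocol abstract and section 8.3 give the same instruction: "Calculate the cost/utility of the protocol of combinations of different drugs, and ascertain the optimal protocol of hospital treatment of patients with acute cerebral stroke". Section 8.3 also fixes the outcome measure: "quality-adjusted life years (QALYs) are used as the index of health outcome".

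The analysis section, 10.5, is one sentence: "The cost - utility evaluation methods are used for the pharmacoeconomic analysis of the drug and the sensitivity analysis for the cost and utility indexes".

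Two other places bear on the reading. The introduction describes the aim as "the seeking of one or more kinds of drug therapeutic regimens with a high price/performance ratio". Section 2 lists the secondary objective only as "Analysis of cost-utility of various drug combinations in treatment of acute ischemic stroke".

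None of these places names an incremental ratio, a comparator, a willingness-to-pay value, an interval, or a result in which no regimen is called optimal.

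**The concern.** A regimen's own cost divided by its own QALYs does not answer the question a decision maker faces when one regimen costs more and does more. That question is what the additional QALYs cost. Most of the QALY total accrues to any survivor whatever drugs were given, so a dearer regimen must raise the whole total in proportion to its extra cost before its average ratio improves. A regimen with a real gain at an acceptable incremental price can therefore rank below a cheaper, less effective one by arithmetic alone.

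Separately, a selection made on point estimates carries no information about whether the chosen regimen differs from the others by more than sampling error. The introduction offers the results to clinicians as a reference for choosing drugs, so an unqualified statement of the optimum matters.

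**Working it through.** The protocol states no figure for this analysis, so there is none to reproduce. All cost and QALY inputs below are assumptions.

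**1. What the average ratio does.** Let the cheaper regimen have mean cost C0 and mean QALY Q0, and the dearer one C0 + ΔC and Q0 + ΔQ. The dearer regimen has the lower average ratio only if

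(C0 + ΔC)/(Q0 + ΔQ) < C0/Q0, that is, ΔC/C0 < ΔQ/Q0, or equivalently ΔC/ΔQ < C0/Q0.

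So the comparison acts as an incremental analysis whose threshold is the cheaper regimen's own average ratio. That threshold comes from the data and the time horizon, not from a stated willingness to pay.

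**2. Misranking without noise.** A: 15,000 RMB for 0.60 QALY, ratio 15,000/0.60 = 25,000. B: 18,000 RMB for 0.70 QALY, ratio 18,000/0.70 = 25,714. The average ratio prefers A. The incremental ratio of B over A is 3,000/0.10 = 30,000 RMB per QALY, so B is preferred at any willingness to pay above 30,000.

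**3. Two regimens with sampling error.** Inputs: n = 1,000 per regimen, C0 = 15,000 RMB, cost CV 0.8, Q0 = 0.65, SD 0.30, Q1 = Q0 + ΔQ. On the log scale:

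d = ln[(C0 + ΔC)/Q1] − ln[C0/Q0]

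SE² = 2·CV²/n + (SD/Q0)²/n + (SD/Q1)²/n

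P(cheaper regimen has the lower ratio) ≈ Φ(d/SE)

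The cheaper regimen's ratio is 15,000/0.65 = 23,077.

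- +1,500 RMB, +0.05 QALY: dearer ratio 16,500/0.70 = 23,571; d = 0.0212; SE = 0.0409; P = Φ(0.52) = 70%. Incremental cost 30,000 per QALY.
- +1,500 RMB, +0.10 QALY: dearer ratio 16,500/0.75 = 22,000; d = −0.0478; SE = 0.0407; P = Φ(−1.18) = 12%. Incremental cost 15,000 per QALY.
- +3,000 RMB, +0.10 QALY: dearer ratio 18,000/0.75 = 24,000; d = 0.0392; SE = 0.0407; P = Φ(0.96) = 83%. Incremental cost 30,000 per QALY.

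With cost CV from 0.5 to 1.2, the three probabilities span 64–76%, 5–20% and 75–91%. Simulation with lognormal costs and normal QALYs at CV 0.8 gave 69%, 12% and 83%.

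**4. Horizon.** A mean of 0.65 QALY needs about a year. The utility pathway written out in 8.3 ends at day 90, where full health gives at most 90/365.25 = 0.246 QALY. Section 8.3 also lists an EQ-5D assessment at day 360, so the horizon is open. With an assumed 90-day mean of 0.17 QALY (SD 0.06), a gain of 0.05 QALY is 29% of the total, and the regimen adding 1,500 RMB almost never loses. The implicit threshold also moves, from 23,077 to 15,000/0.17 = 88,235 RMB per QALY.

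**5. Several regimens.** Eight equal groups from 10,000 patients, 15,000 RMB on average, CV 0.8, 90-day QALY 0.17 (SD 0.06), with the cheapest regimen also the least effective:

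- Costs spread ±20%: the cheapest has the lowest ratio in 94% of runs when the worst-to-best QALY gap is 10%, 85% at 20%, 63% at 30% and 0% at 50%.
- Costs spread ±5%: 13% at a 10% gap and 0% at 20%.

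**The case against.** The strongest reply is that no section says regimens are ranked by their own ratio. The slash may simply name the method, since the protocol elsewhere writes cost-utility, and the methods named in 10.5 can include an incremental analysis. This stands in part: the average-ratio reading is the literal one, but it is an inference that 10.5 does not exclude. It is also fair that reference regimens, thresholds and bootstrap details are often left to an SAP, which is not at hand. Their absence alone would be no finding. What remains is the instruction that the protocol does state, to select an optimum from cost/utility.

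The introduction's wish for one or more regimens softens the idea of a single forced winner, and the objective speaks only of analysis. The planned sensitivity analysis on cost and utility deserves credit, but it is not described as a statement of sampling uncertainty.

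A reader might infer three stronger points that the documents do not support:

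- **The method picks the cheapest regimen regardless of outcome.** It does not. The cheapest loses when QALYs differ relatively more than costs, as the 12% case shows. Where QALYs are truly equal and costs differ, choosing the cheapest is right.
- **Naming a winner among identical regimens proves the rule faulty.** Any minimum or maximum returns a value, including the largest net benefit. The fault is the missing statement of uncertainty.
- **Negative utilities in the tariff make the ratio meaningless.** That would affect ratios formed patient by patient, which no section prescribes.

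**Conclusion.** The point holds as a fault in the stated selection criterion, not as proof of a wrong result. Taken literally, 8.3 and the abstract compare average cost per QALY and report an optimum with no uncertainty attached. In the assumed one-year setting, a regimen whose extra QALYs cost 30,000 RMB each ranks behind the cheaper, less effective one in about 70% to 83% of trials. One whose extra QALYs cost 15,000 RMB each ranks behind it in about 12%. Whether 30,000 RMB is modest depends on a willingness-to-pay value that the protocol does not state. The figures also depend on the number of regimens, the cost and QALY spreads and the horizon, none of which the protocol settles. The change should be made, since it is inexpensive and the result is meant to inform prescribing.

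**What to change.** In 8.3, 10.5 and the abstract, replace selection on cost/utility by an incremental analysis across the drug combinations. Report incremental cost, incremental QALYs, and either the ICER or net monetary benefit (willingness to pay × QALYs − cost) at stated willingness-to-pay values. Add bootstrap intervals and acceptability curves covering all combinations at once, because beating a single reference does not make a regimen best among many.

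Replace the promise to find the optimal protocol by a report of which regimen has the highest expected net benefit, together with its probability of being best. State that the regimens are not distinguishable where the data do not separate them. A significance gate on net benefit is not needed.

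The cost is revised wording and some bootstrap programming, with no new data. The downside is that the analysis may not name one optimal regimen.

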# 5 Treatment regimen

In the study, the doctors can select the specific treatment regimen for cerebral stroke according to the patient's clinical medical history and characteristics of symptoms as well as the China 2011 Guidelines for Diagnosis and Treatment of Ischemic Cerebral Stroke. This study has no limitations on the selection, dose and treatment course of the treatment drugs.

According toChinese Guideline for Diagnosis and Management of Acute Ischemic Stroke2010, The specific treatment on acute ischemic cerebral stroke refers to the intervention with a certain link in the pathophysiological mechanism of ischemic injuries. Examples are given to the following common drugs for illustration:

1. Intravenous thrombolysis drug: rt-PA and urokinase.
2. Anti-platelet drugs: aspirin and Clopidogrel
3. Anticoagulants: including unfractionated heparin, low molecular heparin, ateroid, oral decoagulants and thrombin inhibitor.
4. Volume expansion drug: hydroxyethyl starch, and low molecular dextran.
5. Nerve protective agents: Edaravone, nicholin and ganglioside.
6. Cerebral blood flow perfusion improving drugs: butylphthalide, human urine kininogenase (Urinary Kallidinogenase for Injection).
7. Chinese herbal medicines: Shuxuetong injection, and Danhong injection.

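### QALYs that start from the pre-treatment utility are used to rank doctor-chosen regimens, and the protocol provides no baseline adjustment for that comparison

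*Protocol*

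**What the plan says.** - **Purpose.** Section 8.3 sets the task as "Calculate the cost/utility of the protocol of combinations of different drugs, and ascertain the optimal protocol of hospital treatment". This serves secondary objective (2), the cost-utility of the drug combinations.
- **Utility measurements.** Section 8.3 derives the QALY from EQ-5D utilities "evaluated on day 0 before treatment, at discharge,on 90 ± 14 days after treatment, 360 ± 28 days after treatment". The first value therefore predates any study-recorded therapy.
- **Construction.** The path is formed "by connecting the utility values on day 0, at discharge, on 90 ± 14 days after medication". On weighting, 8.3 adds "With the time required for improving the quality of life as weights, we will get the QALY values", and then "See the reference for the calculation method".
- **Analysis.** Section 10.5 is one sentence: "The cost - utility evaluation methods are used for the pharmacoeconomic analysis of the drug and the sensitivity analysis for the cost and utility indexes". It names no model, estimator or covariate.
- **Allocation.** Under Section 5, "the doctors can select the specific treatment regimen for cerebral stroke according to the patient's clinical medical history and characteristics of symptoms".
- **Other comparisons.** The between-group tests in Sections 10, 10.3, 10.4 and 10.6 are chi-square, Fisher, analysis of variance, Kruskal-Wallis and Wilcoxon tests, none with a covariate. NIHSS and the EQ-5D visual analogue score are at least analysed as change from baseline. The QALY is not described that way.

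**The concern.** The day-0 utility is measured before treatment, yet it is one of the three points that make up the outcome. Because doctors select regimens partly on symptoms, mean day-0 utility can be expected to differ between regimens. The difference reaches the QALY by two routes: directly, through the first segment of the path, and indirectly, because patients who start worse tend to be worse at discharge and day 90 whatever they receive. Neither route reflects a drug effect.

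What is at stake is the ranking. If the totals are compared as they stand, the regimen called optimal may be the one that was given to milder patients. Adjusting the mRS or NIHSS comparisons in 10.3 would not help, since the cost-utility result is produced separately under 8.3 and 10.5.

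**Working it through.** The protocol states no QALY figure, effect size or power, so there is no figure to reproduce. The check asks how much QALY difference arises when the drugs do nothing.

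**Inputs**
- From 8.3: path through day 0, discharge (day L) and day 90, weighted by time.
- From the tariff in 8.3: utility = 1 − 0.152 − sum of decrements.
- Assumed, because the protocol gives no values: stay L = 14 days, day-0 utility gap d = 0.10 between regimens, share r of the gap persisting to discharge and day 90, and a true gain g = 0.03 at discharge and day 90 for comparison.

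**Formulas**
- QALY = [(u0 + ud)/2 × L + (ud + u90)/2 × (90 − L)] / 365
- Spurious difference = [d(1 + r)/2 × L + d·r × (90 − L)] / 365
- Value of the true gain = [g/2 × L + g × (90 − L)] / 365

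**Results, 90-day path**
- Gap gone by discharge (r = 0): 0.05 × 14 = 0.7; 0.7/365 = 0.0019. This is the contribution of the day-0 point alone.
- Half persists (r = 0.5): 0.075 × 14 + 0.05 × 76 = 4.85; 4.85/365 = 0.0133.
- All persists (r = 1): 0.10 × 14 + 0.10 × 76 = 9; 9/365 = 0.0247.
- True gain: 0.015 × 14 + 0.03 × 76 = 2.49; 2.49/365 = 0.0068.
- Ratios to the true gain: 0.7/2.49 = 0.28; 4.85/2.49 = 1.95; 9/2.49 = 3.61.
- Share due to the day-0 point itself: 0.7/4.85 = 14% and 0.7/9 = 8%. The rest is severity carried to later visits.

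**How far the assumptions move this**
- Gap 0.05 instead of 0.10: every ratio halves, to 0.14, 0.97 and 1.81. Gap 0.20: every ratio doubles, to 0.56, 3.90 and 7.23. Doubling the true gain to 0.06 also halves every ratio.
- Stay of 10 days: 0.5/2.55 = 0.20 up to 9/2.55 = 3.53. Stay of 21 days: 1.05/2.385 = 0.44 up to 9/2.385 = 3.77.
- Path extended to day 360, with gain and gap carried forward: the true gain becomes (0.21 + 0.03 × 346)/365 = 10.59/365 = 0.029. The ratios become 0.7/10.59 = 0.07, 18.35/10.59 = 1.73 and 36/10.59 = 3.40.

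**Is a gap of 0.10 plausible on the protocol's own tariff?**
- State 22211: 1 − 0.152 − 0.075 − 0.054 − 0.044 = 0.675.
- State 33311: 1 − 0.152 − 0.418 − 0.102 − 0.133 = 0.195.
- The states differ by 0.480, so a mean gap of 0.10 needs 0.10/0.480 = 21 percentage points more patients in the worse state.

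**Same improvement from different starting points.** Let both states gain 0.1 by discharge and 0.2 by day 90, with L = 14.
- From 0.675: (0.725 × 14 + 0.825 × 76)/365 = 72.85/365 = 0.200.
- From 0.195: (0.245 × 14 + 0.345 × 76)/365 = 29.65/365 = 0.081.
- Difference: 43.2/365 = 0.118 QALY with identical improvement. Above its own day-0 level, each gives (0.05 × 14 + 0.15 × 76)/365 = 12.1/365 = 0.033, a difference of zero.

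**The case against.** **The protocol is silent rather than wrong.** Section 10.5 fixes no method of comparison, and covariates are often left to a statistical analysis plan, which is not shown here. A reader might infer that the protocol positively prescribes an unadjusted QALY comparison. It does not say so, and that reading should not be pressed. What remains is that 8.3 fixes the outcome in detail and the use to which it is put, no section provides for adjustment, and every between-group test that is named lacks a covariate. The protocol refers to a statistical analysis plan only in 10.7, for the interim analysis. Followed as written, the text gives a confounded ranking.

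**The construction is normal.** A reader might infer that starting the curve at day 0 is itself an error. It is not: an area under the utility curve that includes baseline is usual, and the remedy below leaves it unchanged.

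**Most of the bias is ordinary confounding by severity.** This is correct: the day-0 point gives 0.0019 QALY, and the larger figures come from persistence. The root is shared with any unadjusted comparison of these regimens, but the repair for the cost-utility result has to be made in 8.3 and 10.5.

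**The weighting sentence and the cited reference might already subtract baseline.** The wording is unclear and the reference is not available, so this cannot be excluded. Subtraction alone would not settle the matter. With d = 0.10, removing 0.10 × 90 = 9 utility-days leaves (0.7 − 9)/365 = −0.023 if the gap closes, (4.85 − 9)/365 = −0.011 if half persists, and 0 only if all of it persists. The bias would then run against the regimen given to milder patients.

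**Conclusion.** The point stands as a weakness in how the QALY will be compared, not in how it is built. Under the stated assumptions the day-0 point alone adds about 0.002 QALY, and persisting severity brings the total to about 0.013 or 0.025, against about 0.007 for an assumed true gain of 0.03. Baseline imbalance can therefore be a minor fraction of a real effect or exceed it, depending on persistence.

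A reader might take the top ratio of 3.6 as the expected size of the bias. The documents do not support that: gap, gain, stay and persistence are all assumed, and the ratios scale directly with the gap and inversely with the gain. The horizon is also unsettled, since 8.3 lists a day-360 utility but ends the path at day 90. The direction under the path as written, favouring regimens given to milder patients, does not depend on those values as long as some of the gap is present at day 0 and later utilities do not reverse it.

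The consequence is limited to secondary objective (2) and the choice of an optimal regimen. The primary objective is unaffected.

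**What to change.** In 8.3 and 10.5, state that:
- incremental QALYs between regimens are estimated by regressing the patient's QALY on regimen, with day-0 EQ-5D utility as covariate, plus baseline NIHSS and age;
- the adjusted increments are the ones used in the cost-utility result;
- unadjusted QALY totals by regimen are descriptive only;
- confounding by unmeasured factors remains and limits any claim that a regimen is optimal.

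The cost is a few sentences and one regression. Section 7.1 already schedules EQ-5D, NIHSS and age at Visit 1, so no new data are needed. Because the QALY as defined requires a day-0 utility, using that utility as a covariate excludes no patient whose QALY can be calculated.
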